### Statistical analysis

A CONSORT diagram [18] will summarise participant flow through the study, documenting eligibility and recruitment, receipt of intervention or standard care as allocated, and collection of data [19]. Standard statistical summaries (e.g. medians and ranges or means and variances, dependent on the distribution of the outcome) and graphical plots showing correlations will be presented for the primary outcome measure and all secondary outcome measures. Baseline data will be summarised to check comparability between treatment arms, and to highlight any characteristic differences between those individuals in the study, those ineligible, and those eligible but withholding consent. Although missing data is not expected to be a major issue for this study, the nature and pattern of the missingness will be carefully considered — including in particular whether data can be treated as missing completely at random (MCAR). If judged appropriate, missing data will be imputed, and resulting imputed datasets will be analysed and reported, together with appropriate sensitivity analyses. Formal analysis, for example using logistic regression with ‘missingness’ as a response, may also be appropriate and aid interpretation.

The primary outcome will be compared between treatment groups using multi-variant logistic regression analysis, adjusting for participant age, gender and co-morbidity; regression coefficients will be considered to be significant if p-values are less than 0.05 (5% significance level). Estimates of treatment effects will be presented with 95% confidence intervals. Although generally we have no reason to expect that the clustering effects will be important for this study, in reality the data will be hierarchical in nature, with patients naturally clustered into groups. Therefore we propose to account for this by generalizing the conventional linear (fixed-effects) logistic regression approach to a more general mixed-effects modelling. i.e. a random effect is included in the model to account for heterogeneity. This analysis will be presented in addition to the conventional fixed effects model. All analyses will be conducted on an intention-to-treat (ITT) basis, and reported as such; additional per-protocol analyses will be undertaken and reported if these prove to be informative.

Any subsequent amendments to this initial SAP will be clearly stated and justified. Interim analyses will be performed only where directed by the data monitoring committee (DMC). The routine statistical analysis will mainly be carried out using R (http://www.r-project.org/) and S-PLUS (http://www.insightful.com/).

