## Methods

The Northumbria Arthroplasty Suture Study (NASS) is an on-going two-centre double blind randomised controlled trial conducted at Northumbria NHS Foundation Trust, one of the largest elective orthopaedic centres in the UK. The study has been approved by Newcastle and North Tyneside Research Ethics Committee (07/H0901/62) and all participants provide informed http://www.controlled-trials.com/ISRCTN25633145). Johnson & Johnson (UK) has provided partial funding for this trial.

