### Study duration

Recruitment into the trial began in December 2008, all participants are now recruited and the 12-month follow-up stage will be completed in early 2014.

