### Participant allocation

Treatment group allocation is based upon an opaque envelope randomised design utilising the date surgery is performed. This allocation is based on random monthly hospital assignment into one of the two groups, each centre providing one treatment for the whole calendar month. Envelopes were only opened at the start of a month, so allocation was not known at the time of listing. Each month the hospitals would be randomised to either control or intervention. A more optimal conventional randomisation methodology, that is randomly allocating individual study participants to one of the two treatment groups at recruitment, is not possible for this study. It was decided by the study development team that it would not be feasible or practical to attempt to do this in the selected setting. Multiple sutures with a variety of surgeon specific needle types would have been used, so a considerable number of blinded sutures would be needed, with the majority discarded. Equally we would have to store large numbers of each suture in the theatre if randomised individually. Lack of specific local support for randomisation and concerns about the impact on the credibility and fidelity of the study interventions were identified as problematic issues if individual participant randomisation were adopted. Within this study setting the surgeon was not blinded to the sutures. The study participants, research associates involved in recruitment and assessment, and clinical staff involved in the care of study participants were all blind to treatment allocation throughout the study. The statistician is also blinded.

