### Interventions

#### Hip and knee replacement participants

Before the operation, all patients followed the same patient pathway from out patient appointment to operation date. The surgeon will be aware of the suture, which will be used to close all layers of the wound, including the subcutaneous skin in a subcuticular technique if deemed appropriate by the operating surgeon. If a subcuticular skin closure technique is not deemed appropriate then metal clips will be used for the skin layer. Prophylactic parenteral antibiotics prophylaxis at the start of trial was Gentamicin (4.5 mg/kg) and this was changed to Gentamicin (3 mg/kg) and Teicoplanin (400 mg) in February 2009 [15] in line with our trust prophylaxis for primary joint replacement. On the initiation of the study the latest systematic review stated there was insufficient evidence to suggest that there was a significant difference in the efficacy of cephalosporin’s compared with that of teicoplanin or penicillin-derivatives, or that a particular generation of cephalosporin’s was more effective than another [16]. Antibiotics were given as a single dose, within 30 minutes of induction.

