### Sample size calculation

The primary outcome for this trial is SSI based on the HPA defined criteria at 30 days post-operation. Two thousand four hundred patients listed for primary hip or total knee replacement are being recruited into the study, and quasi randomised to the intervention arm or the standard care arm. At the initiation of the study the trusts 12 month audited rate of superficial SSI was 2.25% for hip and total knee replacement, which is within that documented in the literature. This sample size will provide 80% power to detect a reduction of SSI infection from 2.25% to 1%, at the 5% level. This difference represents a significant reduction, which would have an important clinical impact.

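### The primary model omits hospital and calendar time, the two factors by which treatment was allocated

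*Protocol article*

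**What the plan says.** The Participant allocation section describes "random monthly hospital assignment into one of the two groups, each centre providing one treatment for the whole calendar month", and adds: "Each month the hospitals would be randomised to either control or intervention". It does not say whether the two hospitals' draws in a given month were linked, and it describes no balancing within hospital or over time.

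The Statistical analysis section sets the primary model as "multi-variant logistic regression analysis, adjusting for participant age, gender and co-morbidity". The section on pre-operative patient factors also promises adjusted regression, but the factors it names are patient characteristics. Neither place names hospital, calendar time or joint.

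The Statistical analysis section does recognise that the data are hierarchical. It proposes a mixed-effects logistic model with a random effect, to be reported beside the conventional model. It does not say what the random effect groups by, and it states that clustering is not expected to be important.

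On dates: "Recruitment into the trial began in December 2008" and "the 12-month follow-up stage will be completed in early 2014" (Study duration). On background prophylaxis, the Interventions section reports that "this was changed to Gentamicin (3 mg/kg) and Teicoplanin (400 mg) in February 2009".

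**The concern.** An analysis should normally reflect the way treatment was assigned. Here the randomised unit is a hospital-month, so hospital and time are the structure of the allocation. With about 100 units instead of 2400, an arm can easily receive more months from one hospital, or more early than late months. If infection risk differs between the hospitals or drifts over about four years, a model without these terms carries that imbalance into the treatment estimate. At stake is the precision and credibility of the primary result, particularly if it lies close to the significance boundary.

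This is not a detail left to another document. The article states the covariate list and describes its own text as the initial analysis plan.

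**Working it through.** The plan gives no figure of its own on this point, so the check is of how large the effect could be.

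**Inputs from the protocol article.** Two centres; 2400 patients; planned rates 2.25% and 1%; recruitment from December 2008; 12-month follow-up ending in early 2014.

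**Assumptions.** 1:1 allocation (1200 per arm); recruitment ending about early 2013; equal monthly volumes; independent monthly draws at each hospital unless stated; hospital-specific infection rates of 1.5% and 3.0%. The documents give only a pooled rate ("12 month audited rate of superficial SSI was 2.25% for hip and total knee replacement").

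**Number of randomised units.** December 2008 to about early 2013 is about 49 to 51 months. Two hospitals × about 50 months ≈ 100 hospital-months, or about 24 patients each.

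**Expected events.** 1200 × 0.0225 + 1200 × 0.01 = 27 + 12 = 39.

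**Spread of the allocation.** The SD of the share of intervention months at one hospital is √(0.25/50) = 0.071. The difference between arms in the share of patients from a given hospital then has SD about 0.071 × √2 = 0.10.

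**Illustration.** Let the lower-risk hospital give 57% of its months to the intervention and the other 43%, about 1 SD each in opposite directions.
- Intervention arm: 0.57 × 1.5% + 0.43 × 3.0% = 2.145%
- Control arm: 0.43 × 1.5% + 0.57 × 3.0% = 2.355%
- Spurious difference: 0.21 points, and 0.21 / 1.25 = 17% of the planned difference
- Standard error of the planned difference: √[(0.0225 × 0.9775 + 0.01 × 0.99)/1200] = 0.52 points, and 0.21 / 0.52 ≈ 0.4

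**How often.** With 50 months per hospital and independent draws, an imbalance at least this large in either direction has a probability of about 19%. The median absolute shift under the same assumed rates is about 0.09 points.

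**Other hospital contrasts.** With an assumed hospital risk ratio of 1.5, 2 or 3, chance imbalance distorts the treatment risk ratio by a factor of up to 1.09, 1.15 or 1.23 at the 95th percentile (49 months). The planned risk ratio is 1/2.25 = 0.44.

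**How the two draws might be linked.**

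| Monthly draws | Hospital | Calendar time |
|---|---|---|
| Independent | can be unbalanced (SD 0.10) | can be unbalanced |
| Opposite arms | can be unbalanced (SD 0.14) | balanced by design |
| Same arm | balanced by design | each month is wholly in one arm |

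No version balances both factors.

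**Prophylaxis change.** December 2008 and January 2009 at two hospitals make 4 hospital-months, about 4% of 100. Take 50 hospital-months per arm, a base rate of 2.25%, and earlier risk 1.5 or 2 times higher. A 3:1 split then shifts the difference by (2/50) × 0.5 × 2.25 = 0.045 or (2/50) × 1 × 2.25 = 0.09 points. A 4:0 split with doubled risk gives (4/50) × 1 × 2.25 = 0.18 points.

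**Cost in parameters.** Treatment, age, gender and co-morbidity as one term each: 39/4 = 9.75 events per parameter. With hospital and linear time added: 39/6 = 6.5. With joint as well: 39/7 = 5.6.

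**The case against.** The strongest reply is that the plan does not ignore the hierarchy. It offers a mixed-effects model, and a random effect for hospital or hospital-month would cover part of the problem. That deserves weight, but the grouping is unnamed and the model is supplementary. A random effect for two hospitals is poorly estimated, and one for hospital-months widens the interval without removing a hospital difference or a trend.

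Second, the size is modest and conditional. The hospital rates are assumed, 0.21 points needs a roughly one-in-five imbalance, and under the same assumptions the type I error would rise only from 5% to about 5.7%. This stands. A reader might infer that the treatment estimate is biased. The documents do not support that: allocation was random, so over repeated allocations the imbalance averages out.

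Third, the article may simply omit details of balancing or of linked draws. This also stands, but no linking of the two draws in a month protects both hospital and time.

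Two stronger readings are tempting. One is that the February 2009 prophylaxis change seriously confounds the comparison. It falls after only about 4% of hospital-months, its application across both hospitals is inferred from the reference to trust policy, and its plausible effect is small. A linear month term would not capture such a step in any case. The other is that hip versus knee must be in the model. Joint was not an allocation factor and the article gives no joint-specific rates, so adjusting for it is a matter of preference.

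**Conclusion.** The point holds in a limited form. The stated primary model leaves out hospital and calendar time, although treatment was allocated by both, and the supplementary mixed model does not reliably make up for this. The consequence is added noise, or a chance shift, in the realised estimate. Typical shifts are about 0.1 point, with 0.21 points (about 0.4 standard errors) not unusual, if one hospital has twice the infection rate of the other. Such shifts would not overturn a true risk ratio of 0.44, but they could matter for a borderline result.

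The omission itself is plain from the text. The size rests on the assumed hospital rates, about 50 months of recruitment, equal monthly volumes and independent draws.

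**What to change.** Add to the primary logistic model a fixed effect for hospital and one calendar-time term, linear in month of surgery. Record this as a justified amendment before unblinding; the article provides for amendments and says that the statistician is blinded.

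No new data are needed, since site and date of operation determine the allocation. The cost is two parameters, which takes events per parameter from 9.75 to about 6.5, counting co-morbidity as one term (lower if it has several). For the same reason, time should stay a single term: about 50 month effects could not be supported by 39 events.

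Optional additions are a term for joint, and a sensitivity analysis excluding operations before the February 2009 prophylaxis change.

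### Hospital-months are randomised, but the model that respects them is only an additional analysis, its random effect is not tied to the hospital-month, and no rule says which model decides

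*Protocol article*

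**What the plan says.** **Allocation** (Protocol article, Participant allocation): "This allocation is based on random monthly hospital assignment into one of the two groups, each centre providing one treatment for the whole calendar month". The same section says that "randomly allocating individual study participants to one of the two treatment groups at recruitment, is not possible for this study".

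**Primary comparison** (Protocol article, Statistical analysis): "The primary outcome will be compared between treatment groups using multi-variant logistic regression analysis, adjusting for participant age, gender and co-morbidity". The threshold follows: "regression coefficients will be considered to be significant if p-values are less than 0.05 (5% significance level". This model has no term for hospital or month.

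**Clustering** (same section): the sentence begins "Although generally we have no reason to expect that the clustering effects will be important for this study" and goes on to accept that patients fall into groups and that the data are hierarchical. To account for this the authors propose a mixed-effects generalisation of the logistic model, in which "a random effect is included in the model to account for heterogeneity". The grouping unit is not named. On the standing of this model the article says: "This analysis will be presented in addition to the conventional fixed effects model".

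**The concern.** When "each centre providing one treatment for the whole calendar month", everyone operated on at that hospital in that month has the same allocation. Whatever else those patients share (site, staff, period) is then carried into the treatment contrast. An analysis that treats patients as separately allocated takes its standard error from variation between patients and leaves out variation between hospital-months.

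Three features of the text combine:

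- The model introduced as the means of comparing the arms ignores the unit of allocation, and the one that might respect it is an addition.
- The random effect is motivated by natural grouping. A random effect for surgeon or for hospital would satisfy the wording, yet would leave month-to-month variation within a hospital outside the standard error.
- The article sees no reason to expect clustering to matter, although the allocation itself creates clusters.

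At stake is the validity of the primary p-value and interval. Two models face one 5% threshold with no deciding rule, so a borderline result could be claimed from the one that does not match the design.

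**Working it through.** **Inputs from the Protocol article.** 2400 patients; two centres; rates of 2.25% and 1% (Sample size calculation); recruitment from December 2008, with 12-month follow-up ending in early 2014 (Study duration).

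**Assumptions.** 1:1 allocation. Recruitment is taken to end in about early 2013, giving about 50 months × 2 hospitals = 100 hospital-months and 2400/100 = 24 patients in each. The article gives no ICC, so 0.001 to 0.02 is shown.

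**The plan's own figure.** It has none for clustering. Its nearest figure is 80% power, stated without a design effect. With 1200 per arm and pooled variance, SE under the null = √(2 × 0.01625 × 0.98375/1200) = 0.00516 and SE under the alternative = √((0.0225 × 0.9775 + 0.01 × 0.99)/1200) = 0.00516. Two-sided power is Φ((0.0125 − 1.96 × 0.00516)/0.00516) = 67.8%; one-sided at 5% it is 78.2%. The stated 80% is thus approached only by a one-sided calculation for individually randomised patients. That is a separate point, noted here because it shows that no allowance was made for hospital-months.

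**Events per cluster.** 1200 × 0.0225 + 1200 × 0.01 = 27 + 12 = 39 events; 39/100 ≈ 0.4 per hospital-month.

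**Effect on the conventional model.**

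- Design effect: DE = 1 + (24 − 1) × ICC
- True two-sided type I error at nominal 5%: 2 × (1 − Φ(1.96/√DE))
- Factor by which the interval should be wider: √DE
- Corrected p for a conventional p of 0.040 (z = 2.054): 2 × (1 − Φ(2.054/√DE))
- Spread of true hospital-month risk implied by the ICC, as SD/mean at p = (2.25% + 1%)/2 = 1.625%: √(ICC × (1 − p)/p)

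| ICC | DE | Type I error | Interval factor | p = 0.040 becomes | Implied SD/mean |
|---|---|---|---|---|---|
| 0.001 | 1.02 | 5.3% | 1.01 | 0.042 | 25% |
| 0.005 | 1.12 | 6.3% | 1.06 | 0.052 | 55% |
| 0.01 | 1.23 | 7.7% | 1.11 | 0.064 | 78% |
| 0.02 | 1.46 | 10.5% | 1.21 | 0.089 | 110% |

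**Simulation check.** Beta-binomial simulation of 100 hospital-months gave 5.2%, 6.2%, 7.6% and 10.8% at the four ICCs, against 4.9% to 5.6% for a cluster-robust test. A separate simulation with exactly 24 patients in each gave 5.2%, 6.1%, 7.0% and 9.9%, and 4.7% at ICC 0.

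**Sensitivity to cluster size.** With 88 hospital-months (mean 27.3) and a coefficient of variation of 0.4 in size, DE = 1 + ((1 + 0.4²) × 27.3 − 1) × ICC. Type I error is then about 5.35%, 6.8%, 8.6% and 12.3%.

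**The case against.** The strongest reply is that the plan already deals with clustering. A reader who stops at the opening clause might infer that it is dismissed; the rest of the sentence and the next one do not support that. They concede the hierarchy and commit to a mixed-effects model, which is the type of model that this design needs, and both results will be reported.

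A reader might also infer that the conventional model is declared primary. It is not: neither model carries that label. The order of presentation and the word for the mixed model's additional role suggest that the conventional model leads, while the stated intention to account for hierarchy points the other way. What stands is the lack of a deciding rule.

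Third, the grouping variable could be left to a full analysis plan. That is fair for detail alone. But the article itself gives a rationale (natural grouping) that does not match its own allocation, and it treats its analysis text as the initial analysis plan.

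Fourth, the size is uncertain. At ICC 0.001 the inflation is negligible. ICC 0.02 requires true monthly risk to vary by about 110% of its mean, a strong assumption for elective primary joint replacement within one trust. The documented change of antibiotic prophylaxis in February 2009 is a real difference between months, but it came only about two months into recruitment. So a reader should not take the 10.5% figure as the expected error rate.

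Finally, a mixed model may change little. With about 0.4 events per hospital-month, simulation put the between-cluster variance at zero in about 53%, 32% and 15% of trials at ICC 0.001, 0.005 and 0.01, and the mixed model then reduces to the conventional one. This stands, and it bears on the remedy.

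**Conclusion.** The point holds as one about the status and the unit of the cluster model. The article randomises hospital-months, leads with a patient-level comparison, adds a mixed model whose random effect is not tied to the hospital-month, and leaves open which of the two decides.

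The direction is certain for any positive hospital-month ICC: the conventional type I error exceeds 5% and its interval is too narrow. The size cannot be fixed from the documents. It runs from negligible at ICC 0.001 to about a doubling of the nominal error at 0.02, and it rests on the assumed 100 hospital-months of 24 patients. At the intermediate values of 0.005 and 0.01 a conventional p of 0.040 would already cross the 5% threshold. With about 39 events expected, a result close to that threshold is realistic.

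**What to change.** Before unblinding, name one primary analysis that respects the hospital-month: either GEE or cluster-robust standard errors by hospital-month, or a mixed-effects logistic model with a random intercept for hospital-month. In either case include hospital as a fixed effect.

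Because events are sparse and the variance component may be estimated at zero, support it with a permutation test that re-randomises hospital-months by the scheme actually used. The article does not establish whether the two hospitals were drawn independently each month, so that has to be taken from the allocation records.

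Relabel the conventional model as a sensitivity analysis, and delete the clause that sees no reason to expect clustering to matter.

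The cost is a slightly wider interval (a factor of 1.01 to 1.21 over the ICC range shown) and minor extra programming. No new data are needed, since hospital and date of surgery determined the allocation. The article states that recruitment is complete, follow-up is still running and the statistician is blinded, and it allows for justified amendments, so the change can be made without knowledge of the results.
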